### 2.2 Design

A mixed-method, implementation study adopting a multi-centre prospective cohort study design, with nested process and economic evaluations will be conducted. The implementation strategy assessments will be underpinned by the integration of the Consolidated Framework for Implementation Research (CFIR) [13] and Normalisation Process Theory (NPT) [14], which will provide holistic insights into the macro (*i.e.,* system-level) and micro (*i.e.,* individual-level) factors influencing implementation outcomes [15].

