#### 2.2.4 Carers.

The target population of HELP is informal carers of patients with symptomatic HF. These individuals will be eligible to participate if they are: 1) Aged 18 years or older; 2) Physically and mentally capable of operating a digital device; 3) Able to engage comfortably in conversation with peers and capable of reading written materials; 4) Caring (regular, unpaid care) for a person with a clinical diagnosis of HF who is receiving standard evidence-based HF therapies and has either HF symptoms or one episode of decompensation (symptoms requiring medical attention) in previous six months; and 5) Capable of speaking and understanding English.

There will be five programme rollouts of HELP (six weeks each) across each of the three collaborating nations over a one-year period, with twelve carers per rollout (60 carers per nation; 180 carers in total). This sample size was pragmatically determined by the maximum study duration within the funding limit, along with the recruitment rate demonstrated in the pilot study [10].

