#### 2.2.5 Patients.

Patients who are receiving informal support from the recruited carers will be invited to participate via the provision of data, which will allow their perspectives on HELP implementation to be captured, whilst also facilitating an assessment of the potential, dyadic impact of the intervention. These patients will be eligible to participate if they are: 1) Aged 18 years or older; 2) Physically and mentally able to engage comfortably in conversation and capable of reading written materials; 3) Clinically diagnosed with HF and receiving standard evidence-based HF therapies and either have HF symptoms or one episode of decompensation (symptoms requiring medical attention) in previous six months; 4) Able to speak and understand English; and 5) Receiving regular, unpaid support with managing their condition from a loved one (*i.e.,* a relative or spouse) or friend. Patients will be ineligible if their carers refused to participate in HELP. Carers will remain eligible for participation regardless of patient enrolment. One patient per carer will be invited to participate to enhance sample diversity (approximately 180 patients in total).

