### 2.5 Data analysis

#### 2.5.1 Quantitative data.

Quantitative data analysis will be managed on Statistical Package for the Social Sciences (IBM SPSS Statistics, Version 31). Continuous data will be presented as mean ± standard deviation, with discrete data reported as absolute numbers and percentages. Categorical data will be displayed as frequency/ percentages. For participant outcomes, repeated measures analysis of variance will be used to investigate the effect of time point on outcome scores. Due to the absence of statistical power, the results will be used to identify preliminary evidence of promise for the intervention across different participant outcomes, with potential effect sizes generated to inform the required sample size for a future definitive evaluation.

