### 3.1 Strengths and limitations

This mixed-method, implementation study will subject a novel, co-designed intervention to real-world process and economic evaluations across three nations of the UK (Northern Ireland, England, and Scotland). Underpinned by implementation science frameworks (CFIR and NPT) [13,14], the holistic findings will underscore key factors influencing successful translation to clinical settings. The collaborating hospital sites cover a range of settings and characteristics (*i.e.,* urban, rural, education level, socio-economic status, and ethnicity), which will maximise the diversity of the recruited sample. Through establishing beacon sites, the study will facilitate a real-world, clinical platform to model programme implementation, which will support future scaling. Whilst the study is limited to English-speaking participants, the Steering Group will ensure HELP is optimised for future language translation. Whilst digital access was not a barrier to participation in the pilot study [10], we have a stock of digital devices to provide to those without access in the current study. Given the non-randomised design and lack of statistical power, the participant outcomes will not represent definitive findings. This assessment will be conducted in a future study. Finally, HELP is currently limited to carers, future work will expand this intervention to include patients.

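### Effect sizes from an uncontrolled change over time are planned as input to the definitive sample size, and section 2.5.1 names lack of power, not lack of a comparator, as the limitation

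*Protocol article*

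**What the plan says.** Section 2.2 sets out a single-cohort design: "A mixed-method, implementation study adopting a multi-centre prospective cohort study design, with nested process and economic evaluations will be conducted". No comparison group is described, and the Abstract has all recruited carers receiving the programme. Section 2.3.4 measures participant outcomes at baseline, week six and six months post-intervention.

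For these outcomes, section 2.5.1 states that "repeated measures analysis of variance will be used to investigate the effect of time point on outcome scores". It then gives the caveat and the purpose: "Due to the absence of statistical power, the results will be used to identify preliminary evidence of promise", "with potential effect sizes generated to inform the required sample size for a future definitive evaluation". Section 3.0 describes the next step as a large type 2 hybrid effectiveness-implementation study.

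Section 3.1 gives a broader caveat: "Given the non-randomised design and lack of statistical power, the participant outcomes will not represent definitive findings".

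The size of the cohort is fixed in section 2.2.4, "with twelve carers per rollout (60 carers per nation; 180 carers in total"), on pragmatic grounds: "This sample size was pragmatically determined by the maximum study duration within the funding limit, along with the recruitment rate demonstrated in the pilot study". Section 2.2.5 covers the patients: "One patient per carer will be invited to participate to enhance sample diversity (approximately 180 patients in total").

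**The concern.** The time effect is the total change in people who all received HELP. Part of that change may have nothing to do with HELP:

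- **Regression to the mean.** Section 2.2.4 admits carers whose patient has current symptoms or a decompensation in the previous six months, so some will enter at a bad moment.
- **Natural course and other care** over a follow-up that runs to six months after the programme.
- **Repeat testing** on the same questionnaires.
- **Selective retention**, if those who stay differ from those who leave.

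A controlled definitive evaluation needs a difference between groups. Section 2.5.1 gives no route from the change over time to such a difference, and it does not place the target difference on any other footing.

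The caveat in that section also points the wrong way. If low power were the problem, more participants would cure it. More participants only make a confounded change more precise. What is at stake is the size of the next study, and how any sign of promise in this one is read.

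**Working it through.** **1. The plan's own figure.** 5 rollouts × 12 carers × 3 nations = 180 carers, as stated. Section 2.2.4 gives no alpha, power, effect size or SD, so there is no power figure to reproduce.

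**2. Is power for within-carer change really absent?** Take one paired contrast, such as baseline to week six, two-sided 5%, normal approximation. The smallest standardised change (mean change divided by SD of change) with 80% power is (1.96 + 0.8416)/√n = 2.8016/√n.

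- n = 180: 2.8016/13.416 = 0.21.
- n = 126 (30% loss, assumed): 2.8016/11.225 = 0.25.

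HELP is delivered in groups of about twelve (section 2.2.8), so changes may be correlated within a group. With design effect 1 + 11 × ICC and n = 180, the detectable change is 2.8016 × √(design effect/180). With 126 completers (8.4 per group) the design effect is 1 + 7.4 × ICC. The ICC is assumed.

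| ICC | Design effect, n = 180 | Detectable change, n = 180 | Detectable change, n = 126 |
|---|---|---|---|
| 0.01 | 1.11 | 0.22 | 0.26 |
| 0.05 | 1.55 | 0.26 | 0.29 |
| 0.10 | 2.10 | 0.30 | 0.33 |

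Power to detect within-carer change is therefore reasonable. This does not carry over to patients: they are invited, carers may take part without them (section 2.2.5), and their number is uncertain.

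**3. What happens if the observed change is used as the target difference?** Assumptions, none of them from the documents: a two-arm 1:1 trial, SD 1, two-sided 5%, 80% power, and an observed change of 0.40 SD.

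- Planned size: 2 × 2.8016²/0.40² = 15.70/0.16 = 98.1, so 99 per arm.
- True difference: 0.40 × (1 − share of the change not due to HELP).
- Actual power: Φ(true difference × √(99/2) − 1.96), where √49.5 = 7.036.

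| Share not due to HELP | True difference | Power at 99 per arm | Per arm needed for 80% |
|---|---|---|---|
| 0% | 0.40 | 80% | 99 |
| 25% | 0.30 | 56% | 175 |
| 50% | 0.20 | 29% | 393 |
| 75% | 0.10 | 10% | 1570 |

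The power loss depends on the share and hardly at all on the starting value: with 0.30 or 0.50 in place of 0.40, the powers are again about 56%, 29% and 10%.

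**4. The opposite direction.** Suppose untreated carers would worsen by 0.10 SD (assumed) while the cohort improves by 0.40. The true difference is then 0.50, and 15.70/0.25 = 62.8, so 63 per arm would do. The planned 99 would be more than needed.

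**The case against.** The best defence is that the authors already know this. Section 3.1 names the non-randomised design beside lack of power, outcome impact is only an exploratory objective (section 1.2), and the effect sizes are called potential and are to inform the later calculation. The later study will also need its own justification. All of that stands. A reader might infer that the observed change will fix the next sample size, and the text does not say so. What remains is that section 3.1 uses the design limitation only to say that the outcomes are not definitive. It is not tied to the sample-size use in section 2.5.1, where power is the only caveat.

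Lack of power can also be read as saying that no power calculation was done, which is true of section 2.2.4. But it is offered as the reason for caution, and for within-carer change it is not the main one.

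Three stronger readings are tempting and not supported:

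- **That the next trial will be under-sized.** The share of change not due to HELP is unknown. Section 1.0 describes self-management becoming harder as heart failure progresses, so untreated carers might worsen and the change might understate the benefit.
- **That any small background drift would be significant with 180 carers.** For a drift of 0.10, the probability is Φ(0.10 × 13.416 − 1.96) = 27%. For 0.20 it is about 77%, and lower with losses or clustering.
- **That a paired effect size is bound to overstate the between-arm effect.** The measure is not specified. With baseline-to-follow-up correlation r, an unadjusted comparison turns a paired 0.30 into 0.30 × √(2(1 − r)), which is 0.23 at r = 0.7. A baseline-adjusted comparison gives an effective 0.30 × √(2/(1 + r)) = 0.33, so the direction reverses.

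**Conclusion.** The point holds in a limited form. Section 2.5.1 offers an uncontrolled time effect as an input to a definitive sample size, and such an effect does not estimate what that calculation needs. The main limitation for carers is the absence of a comparator. Power for within-carer change is reasonable: 80% at about 0.21 with all 180, 0.25 with 126 completers, and 0.22 to 0.30 with 180 carers and a group ICC of 0.01 to 0.10 (loss and ICC assumed).

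The possible consequence is large but not determined by the documents. Power could fall from 80% to 56%, 29% or 10% for shares of 25%, 50% or 75%, or the next study could be larger than necessary. These figures rest on an assumed two-arm design, an assumed change and assumed shares. The implementation, process and cost objectives are unaffected.

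**What to change.** Reword section 2.5.1 so that it does four things:

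1. States that changes over time in this single cohort do not estimate a between-group effect, and reports them as mean changes with 95% confidence intervals.
2. Names as planning inputs for the definitive study the outcome SD, the baseline-to-follow-up correlation, the rollout-group ICC, uptake and retention.
3. Says that the target difference of the definitive study will rest on a justified minimal important difference and not on the observed change.
4. Gives the absence of a comparator as the main limitation, in line with the design caveat in section 3.1.

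The cost is wording only. The inputs come from data already planned: the three outcome time points, rollout membership, and the screening and recruitment logs of section 2.2.2. No participant procedure changes. The downside is that the study no longer supplies an effect size for planning, so the team must justify a minimal important difference from elsewhere. The ICC will come from only 15 groups (5 rollouts × 3 nations) and should be carried forward with its uncertainty.

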#### 2.5.2 Qualitative data.

Qualitative data will be managed on NVivo (QSR International Pty Ltd. Version 15). Transcripts will be analysed using adaptive framework analysis [34] based on the CFIR and NPT domains [13,14], whilst allowing the integration of data that could not be placed in pre-specified categories. An a priori codebook will be established to guide the analysis. Definitions of CFIR and NPT domains will be tailored to the project, which will improve coder consistency. A member of the central research team will undergo data familiarisation before mapping major themes to the CFIR and NPT domains. Anonymised quotes from participants will be used to support the generation of themes. Differences between and within regions will be compared. A second member of the central research team will independently analyse and verify a random selection of transcripts. Subsequently, the results will be reviewed by the wider project team, with discrepancies discussed until consensus agreement.

#### 2.5.3 Data integration.

Data integration will be conducted according to the recommendations of Farmer et al. [35]. Guided by CFIR and NPT domains [13,14], this integrative analysis will involve the development of a convergent coding matrix to identify synergies (key findings) across the analytic components (*i.e.,* acceptability, fidelity, context, and participant outcomes). Two members of the central research team will integrate quantitative and qualitative data separately, with discrepancies discussed and reviewed by the wider project team until consensus agreement.

#### 2.5.4 Economic analysis.

HELP delivery costs will be estimated according to resource utilisation data collected during the project and unit costs for resource use obtained from published national or National Health Service sources [36]. Resource use will consist of time input from HELP facilitators, supervision for facilitators, training costs for facilitators, and consumables/ adaptations required for HELP delivery. Delivery costs will be estimated at session and programme-level and reported in pounds sterling (£).

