### 1.2 Objectives

1)Evaluate the multi-faceted implementation strategy via a process evaluation of acceptability, fidelity, and context of HELP delivery across real-world clinical sites.2)Estimate the economic cost of HELP implementation.3)Explore the short and long-term impact of HELP on outcomes for carers and patients.

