#### 2.2.9 Intervention delivery.

HELP will be delivered by local specialist HF nurses across the collaborating sites. Following recruitment, carers will be assigned a start date for HELP. One week prior to the first online support group session, carers will receive the educational booklet and access to the supplementary website, along with supporting programme materials (*i.e.,* online support group schedule and guidance on joining online sessions). Carers will be advised to read each chapter of the educational booklet and supplementary website before the corresponding online support group session. The online support group sessions will run on ‘Zoom’, with a link and password to each session issued to carers before commencement. Carers will receive a reminder email two days before each online support group session. The research team will remain in contact with all participants to provide ongoing support with accessing the online support group sessions and supplementary website.

The nurse-led, online support group sessions will be delivered using an informal approach to facilitate a comfortable environment for the carers. Each session will consist of twelve carers and last approximately sixty minutes. The sessions will initiate with a standardised, educational presentation (approximately 20 minutes) on the allocated topic, with the remainder of the session (approximately 40 minutes) dedicated to questions raised during the session or submitted via the website; group discussion; tailored advice and signposting; and peer support. Carers will receive the option of having their cameras switched on or off during the sessions and will be encouraged to use the chat function to ask questions if unwilling to speak in front of the group.

Five programme rollouts of HELP (six weeks each) will be delivered across each of the three collaborating nations over a year period, with twelve carers per rollout (60 carers per nation; 180 carers in total). Rollouts will be separated by four-week windows, which will account for staff holidays and provide recruitment intervals for the subsequent rollout.

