#### 2.2.10 Implementation strategy.

The development of implementation strategies is an evidence-based method of promoting uptake of a novel intervention by healthcare professionals [21]. Accordingly, guided by the NPT framework [14], we engaged with healthcare professionals (approximately forty HF nurses and cardiologists) across our five collaborating sites in the UK to co-develop a multi-faceted implementation strategy for HELP, which is theoretically grounded across: 1) Coherence (*i.e.,* does the intervention make sense?), 2) Cognitive participation (how do people engage?), 3) Collective action (how do people work with the intervention?), and 4) Reflexive monitoring (how do people appraise the intervention?). This iterative, developmental process spanned three, one-hour stakeholder meetings, resulting in the identification of four principal implementation agents (1. HELP Delivery Staff, 2. Referral staff, 3. Clinical Leadership, and 4. Carers). A multi-faceted implementation strategy was developed based on clinical and academic input, which employs tailored methods of supporting HELP implementation for each of the implementation agents (S4 Table).

Depending on preference, intervention delivery staff will receive online or in-person training from the project team, which will employ an interactive approach including content talks, case scenario discussions, and role plays. This training programme will familiarise delivery staff with intervention design and cover essential skills for implementation (*i.e.,* effective communication, building trusting relationships, managing conflict, and delivering behaviour change techniques). These staff will also receive access to standardised intervention materials and support documents (*i.e.,* intervention protocol and fidelity checklist), with regular support and monitoring by the project team at and between Steering Group meetings. As detailed in S4 Table, the other key implementation agents (*i.e.,* HELP referral staff, clinical leadership, and carers) will be supported via communication with the research team, information from project documents (*i.e.,* screening log and information sheets), and monitoring at Steering Group meetings.

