#### 2.3.3 Economic evaluation.

The economic cost of intervention implementation in the UK will be estimated via the collection of the following data from implementation and HELP delivery staff logs:

1)Training costs and time input for supervision of HELP delivery staff.2)The time, expenditure, resources required, and adaptations made for HELP implementation by delivery staff.

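### Objective 2 promises the cost of implementing HELP, but neither the logged items nor the cost list covers the research team's access support to carers, so the figure will be too low

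*Protocol article*

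**What the plan says.** Section 1.2 gives Objective 2 as "Estimate the economic cost of HELP implementation". Section 2.3.3 repeats that target and names two groups of items to be taken from the implementation and delivery-staff logs: "Training costs and time input for supervision of HELP delivery staff" and "The time, expenditure, resources required, and adaptations made for HELP implementation by delivery staff".

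Section 2.5.4 turns these into an analysis. It values resource use at published national or NHS unit costs and defines that use by an exhaustive list: "Resource use will consist of time input from HELP facilitators, supervision for facilitators, training costs for facilitators, and consumables/ adaptations required for HELP delivery". The output has a different name from the objective: "Delivery costs will be estimated at session and programme-level and reported in pounds sterling".

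Section 2.2.9 describes a further input to running the programme: "The research team will remain in contact with all participants to provide ongoing support with accessing the online support group sessions and supplementary website".

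**The concern.** The quantity promised is an implementation cost. The quantity that the rules produce is a delivery cost built from facilitator time, the supervision and training of facilitators, and consumables or adaptations. Help for carers in getting into the sessions and onto the website is supplied by people outside that list. In the study the research team absorbs this work. In a routine service someone else would have to do it, or carers would go without.

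The article says that the findings will inform a larger hybrid study and advance HELP towards routine rollout (section 3.0), and that dissemination should draw attention to what scaling requires (section 2.7). A cost presented as that of implementation, with one running input set to zero, would mislead in one direction only. Because the gap lies in the logging as well as in the analysis, it cannot easily be repaired afterwards: staff time that was not recorded when spent is hard to reconstruct.

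**Working it through.** The article states no cost, unit cost or staff-hour total, so there is no cost figure to reproduce. The planned volume does reproduce: 3 nations × 5 rollouts × 12 carers = 180 carers, which is 15 rollouts, and 15 × 6 = 90 sessions.

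The main check sets the activities that the article describes against the two places that define cost.

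| Activity | Described in | Done by | Logged (2.3.3) | Costed (2.5.4) |
|---|---|---|---|---|
| Running the sessions | 2.2.9 | Heart failure nurses | Yes | Yes |
| Training and supervising delivery staff | 2.2.10 | Project team | Yes | Yes |
| Helping carers with access | 2.2.9 | Research team | No | No |
| Session reminders | 2.2.9 | Not stated | Only if delivery staff do it | Only if delivery staff do it |
| Identifying and approaching participants | 2.2.6 | Local cardiology teams | No | No, but it happens in routine appointments and is partly study recruitment |
| Devices for carers without access | 3.1 | – | Possibly, as resources or expenditure | Possibly, as consumables |

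One row is clearly programme work, clearly done by people outside the list, and clearly absent from both sections: access support to carers.

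**Direction.** Let C be the cost under the list and S ≥ 0 the cost of access support. Then implementation cost ≥ C + S ≥ C, with strict inequality as soon as any support is given. The reported C is therefore too low as an implementation cost.

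**Size.** The documents do not give it. The following illustration is in hours per rollout of 12 carers, and every time except session length is assumed.

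- Counted facilitator time: six 60-minute sessions = 6 h, plus 0 to 2 h of preparation per session (assumed), gives 6 + 6 × 0 = 6 h to 6 + 6 × 2 = 18 h.
- Research-team support at 5 to 30 min per carer (assumed): 12 × 5/60 = 1 h to 12 × 30/60 = 6 h.
- Omitted share of hours, support alone: from 1/(1 + 18) = 5% to 6/(6 + 6) = 50%.
- Adding referral time of 5 to 20 min per carer (assumed): 12 × 10/60 = 2 h to 12 × 50/60 = 10 h omitted. The share runs from 2/(2 + 18) = 10% to 10/(10 + 6) = 62.5%.

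These are shares of hours, not of money. They leave out training, supervision and consumables, which are costed and would lower them. The width of the range shows that the plan gives no basis for a point value.

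**The case against.** The best defence is that the omission is narrow and visible. Section 2.5.4 calls its output delivery costs and says what they contain, so an attentive reader can see the scope. The project team's training and supervision of nurses is counted. The log templates are not shown and might capture more than is listed. The study feeds a later hybrid study and is not offered as a commissioning budget. Much of this stands, and it limits the point. It does not remove it: the objective and section 2.3.3 both say implementation, the second logged item is confined to delivery staff, and the two cost sections agree with each other on the narrow scope.

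A reader might be tempted to go further in several ways that the documents do not support.

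- *The missing hours match or exceed facilitator time.* This would rest wholly on assumed support hours, set against contact time alone and ignoring preparation, supervision and training.
- *The time of clinical leadership is missing.* Section 2.2.10 names "four principal implementation agents (1. HELP Delivery Staff, 2. Referral staff, 3. Clinical Leadership, and 4. Carers"), but the article describes support given to leadership, not labour by it. Being named an agent is no costing rule, since carers are named too.
- *Referral work is a substantial omission.* Section 2.2.6 places it in routine appointments, and part of it is study recruitment, so the added service time may be small.
- *Devices are left out.* Section 3.1 says "we have a stock of digital devices to provide to those without access in the current study". These may fall under consumables or resources, so the article is unclear on them but does not exclude them.
- *Reporting by session and programme hides poor attendance.* Section 2.3.2 records attendance as part of dosage, so a cost per attending carer can be derived.

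**Conclusion.** The point holds in a limited form. The stated target is the cost of implementation, while the logged items and the exhaustive resource list cover delivery-staff inputs, their training and supervision, and consumables or adaptations. Research-team access support to carers is part of running HELP and is costed at zero, so the result will understate implementation cost.

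The direction rests on two things: that support is in fact given, as section 2.2.9 says it will be, and that a service would need to replace it. The size is unknown, and the ranges above are illustrations under assumed times, not estimates. It is worth acting on because it affects one of three objectives, the error runs one way, and the remedy is cheap if made in time.

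**What to change.** Before data collection begins (expected on 01/04/2026, section 2.8):

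1. Add to the implementation log the research-team time spent on carer access support, and on reminders and session hosting if the research team does these.
2. Add any referral-staff time beyond routine appointments.
3. Keep out research-only tasks: consent, eligibility contact and questionnaires.
4. State that devices supplied to carers count as resources.
5. Extend the list in section 2.5.4 to match, value the additions at the same national or NHS unit costs, and report the cost with and without them.
6. Optionally, report cost per carer enrolled and per carer attending, using the attendance already recorded.

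If the sponsor prefers not to collect this, the minimum is to reword Objective 2 and section 2.3.3 as delivery cost only.

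The price is a few log fields, a short tally by referral staff where it applies, some wording, and a somewhat higher reported cost.
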